# Protocol

This trial protocol has been provided by the authors to give readers additional information about the work.

Protocol for: [name], [name], [name], et al. Live birth with or without preimplantation genetic testing for aneuploidy. N Engl J Med 2021;385:2047-58. DOI: 10.1056/NEJMoa2103613

There is the only one version of the protocol, and the implementation process of this trial was strictly in accordance with it.

The statistical analysis plan was finalized before starting enrollment, and was described in section STATISTICAL CONSIDERATIONS (Page 39-40) of study protocol, and as follows:

The primary analysis will be performed in accordance with the principle of intent-to-treat. Continuous variables will be described as mean  $\pm$  standard deviation for the normally distributed variables and as median and range for the non-normally distributed variables. Category variables will be presented as frequency and percentage. The differences in the cumulative live birth rate in the two treatment arms will be compared by absolute risk difference and its 95% confidence interval (CI). The relative risk and its 95% CI will also be calculated. Non-superiority of PGS to IVF will be considered to be established if the upper limit of the 95% CI of absolute risk difference was shown to lie below the non-superiority margin of 7%.

The differences in the secondary outcomes such as rate of good birth outcome, cumulative pregnancy rate, cumulative pregnancy loss rate, multiple pregnancy rate, obstetric and neonatal complications will be tested by Pearson chi-square analyses. The absolute difference and 95% CI as well as relative risk and 95% CI will also be calculated. The difference between duration of pregnancy, birth weight and times of embryo transfer will be tested by student t test and non-parameter test if necessary.

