### **Sample Size and Population**

03/07/2017

We aim to enroll good-prognosis women who are undergoing their first cycle of IVF. The targeted population is women age 20 to 37y, with 3 or more good-quality blastocysts obtained on day 5 of embryo culture. The exclusion criteria are women with a uterine cavity abnormality or women who plan to undergo preimplantation genetic diagnosis (PGD). Given the likelihood of a high proportion of mosaic embryos in the PGS group and our decision to not transfer mosaic embryos (which are unlikely to achieve live birth and have an unknown risk-benefit ratio), we assume that the cumulative live birth rate after the transfer of PGS-selected euploid blastocysts will unlikely exceed that after serially transferring all the 3 untested blastocysts. This study is therefore designed as a non-superiority study. It is estimated the cumulative live birth rate after 3 single embryo transfers is 65% in each group. To be 80% certain that the upper limit of a one-sided 95% confidence interval (CI) would exclude a difference in favor of the PGS group by more than 7%, 575 patients are required in each group. In consideration of 5% drop-out rate, a total of 1208 subjects will be enrolled. The randomization will be stratified by study site. Blocked randomization will be used with dynamic block size. The random number sequence will be generated by the data coordinating center and will be unknown to all investigators. The randomization will be performed on day 5 of embryo culture via a central online randomization system. At present, 8 centers have volunteered and qualified to participate in subjects' enrollment. It is planned that each center will approximately enroll 80 subjects.

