## 9.3 Sample Size and Accrual

Given the possibility of false positive and the decision of not transferring mosaic embryos which are probably to develop into live birth, we assume that the cumulative live birth rate after transferring PGS-selected euploid embryos will be similar with that after serially transferring all the 3 untested blastocysts. This study is designed as a non-superiority study. It is estimated the cumulative live birth rate after 3 single embryo transfers is 65% in the IVF control group. We set a non-superiority margin at an absolute difference of 7% to retain approximately 90% of the clinical effect of the control group. To be 80% certain that the upper limit of a one-sided 95% confidence interval (CI) of absolute difference between groups to reject null hypothesis that PGS is superior to conventional IVF, 575 pa-

tients were required in each group. In consideration of 5% drop-out rate, a total of 1208 subjects will be enrolled. At present, 8 centers have volunteered and qualified to participate in subjects' enrollment. It is planned that each center will approximately enroll 150 subjects.

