#### 9.5 Data Analyses

The primary analysis will be performed in accordance with the principle of intent-to-treat. Continuous variables will be described as mean  $\pm$  standard deviation for the normally distributed variables and as median and range for the non-normally distributed variables. Category variables will be presented as frequency and percentage. The differences in the cumulative live birth rate in the two treatment arms will be compared by absolute risk difference and its 95% confidence interval (CI). The relative risk and its 95% CI will also be calculated. Non-superiority of PGS to IVF will be considered to be established if the upper limit of the 95% CI of absolute risk difference was shown to lie below the non-superiority margin of 7%.

The differences in the secondary outcomes such as rate of Good Birth Outcome, cumulative pregnancy rate, cumulative pregnancy loss rate, multiple pregnancy rate obstetric and neonatal complications will be tested by Person chi-square analyses. The absolute difference and 95%CI as well as relative risk and 95% CI will also be calculated. The difference between duration of pregnancy, birth weight and times of embryo transfer will be tested by student t test and non-parameter test if necessary.

The tertiary outcomes such as the rates of pregnancy, pregnancy loss and live birth after the first transfer will be analyzed with Pearson chi-square test. Cost-effectiveness analysis will be done by decision analytic model with TreeAge Pro 2014 (2014 Version; TreeAge

software). Cost effectiveness is defined as an incremental cost effectiveness ratio (ICER). The ICER for live birth was calculated as the difference in cost between two treatment groups divided by the difference in live birth rates between the two groups. The secondary analysis will be performed according to per-protocol analyses. The primary and secondary outcomes will be compared according to actual treatment that subjects received and among subjects who complete embryo transfer(s).

Subgroup analyses will be performed according to different stimulation protocol (e.g. agonist long, agonist short, and antagonist protocol), different endometrial preparation protocol for FET (e.g. natural ovulation cycle and artificial cycle), age groups (e.g. 20~30 group, 30~35 group and >35 group), with or without history of recurrent spontaneous abortion.

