Any deviations from the previously described statistical plan will be described and justified in a protocol amendment.

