**Final statistical analysis**

Given the possibility of false positive and the decision of not transferring mosaic embryos which are probably to develop into live birth, we hypothesized that the cumulative live birth rate after the transfer of PGT-A-selected euploid blastocysts is not clinically better than that after serially transferring all the 3 untested blastocysts. This study was therefore designed as a non-superiority study. It was estimated the cumulative live birth rate after 3 single embryo transfers was 65% in each group. To be 80% certain that the upper limit of a one-sided 95% confidence interval (CI) would exclude a difference in favor of the PGT-A group by more than 7%, 575 patients were required in each group. In consideration of 5% drop-out rate, a total of 1,208 patients were needed.

Continuous baseline characteristics of PGT-A and IVF groups were represented as means  $\pm$  SD, and between-group differences were compared by Wilcoxon rank-sum test. Categorical variables were represented as frequencies and percentages, and compared by chi-square test. Fisher's exact test was performed for the number of frequencies less than five. Non-superiority test was used to evaluate the absolute rate differences with a two-sided 90% CI for the primary hypothesis only. Other categorical variables were analyzed by estimation of absolute rate differences and relative rates with a two-sided test. Kaplan-Meier curves were used for the time to live birth. We also conducted secondary analyses based on actual treatment that the patients received, the initial, secondary and third embryo transfer in PGT-A and IVF groups. Subgroup analyses were performed according to different endometrial preparation protocol for frozen embryo transfer and age groups. Two-sided P value of  $<0.05$  were considered significant. All analyses were performed using SAS software (version 9.4, SAS Institute).

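### The sample size assumes a one-sided 95% limit but section 9.5 decides on an unqualified 95% CI, under which power is about 70–72%, not 80%

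*Combined protocol and SAP*

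**What the plan says.** Two parts of the protocol describe the primary test.

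- **Sizing.** Section 9.3 reads "To be 80% certain that the upper limit of a one-sided 95% confidence interval (CI) of absolute difference between groups", followed by the figure of 575 per group. The synopsis (Sample Size and Population) has the same basis: "the upper limit of a one-sided 95% confidence interval (CI) would exclude a difference in favor of the PGS group by more than 7" points. The control rate is given in 9.3: "It is estimated the cumulative live birth rate after 3 single embryo transfers is 65% in the IVF control group". The synopsis assumes 65% in both groups. The margin is 7 points and the total, with 5% drop-out, is 1208.
- **Decision.** Section 9.5 reads "Non-superiority of PGS to IVF will be considered to be established if the upper limit of the 95% CI of absolute risk difference" is below 7%. The statistical text at the front of the document, described as finalised before enrolment began, has the same wording. Neither says one-sided or two-sided.

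The section headed Final statistical analysis repeats the one-sided 95% sizing and then reports: "Non-superiority test was used to evaluate the absolute rate differences with a two-sided 90% CI for the primary hypothesis only". The Summary of changes says that the interval had been 95% in the original plan. It gives no reason and no date.

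On departures from the plan, 9.5 ends: "Any deviations from the previously described statistical plan will be described and justified in a protocol amendment". The opening text says: "There is the only one version of the protocol".

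**The concern.** The upper limit of a one-sided 95% CI is the upper limit of a two-sided 90% CI. It is lower than the upper limit of a two-sided 95% CI. If 9.5 means the ordinary two-sided interval, the plan sizes the trial for one test and decides by a stricter one.

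Three things support the two-sided reading of 9.5, although the word is not there:

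- The same paragraph first says that the arms will be compared by the risk difference and its 95% CI, and the decision rule refers back to that interval.
- Where the authors mean one-sided (synopsis, 9.3, Final statistical analysis), they write it.
- The Summary of changes treats the move to a two-sided 90% CI as a change. Had 9.5 meant a one-sided 95% limit, the decision limit would have stayed the same.

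The stakes are the stated power and the probability of wrongly ruling out a 7-point benefit of PGS. Both depend on which section governs.

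**Working it through.** **Inputs.** Live birth 65% in each group (synopsis; 9.3 gives 65% for control); margin 0.07 (9.3, 9.5); power 80% (9.3); 1:1 allocation (9.1); 575 per group and 1208 in total (synopsis, 9.3); denominator all women randomised (9.2.1).

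**Step 1: reproduce the plan's figure.** With a true difference of zero,

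n per group = (z_alpha + z_power)² × 2 × 0.65 × 0.35 / 0.07², where 2 × 0.65 × 0.35 = 0.455.

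- One-sided 5%: (1.6449 + 0.8416)² × 0.455 / 0.0049 = 574.1, so **575**. This is the stated figure.
- One-sided 2.5% (two-sided 95% CI): (1.9600 + 0.8416)² × 0.455 / 0.0049 = 728.8, so **729**.

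Pooled-variance formulas for 72% against 65% give 544 (one-sided 5%), 572 (the same with continuity correction) and 691 (two-sided 5%). None of these gives 575.

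Drop-out: 575 × 1.05 = 603.75, so 604 per group and 1208 in total, as stated.

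**Step 2: power under each rule.** Power = Φ(0.07/SE − z), with SE = √(0.455/n).

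| n per arm | SE | 0.07/SE | One-sided 5% (two-sided 90% CI) | One-sided 2.5% (two-sided 95% CI) |
|---|---|---|---|---|
| 575 | 0.02813 | 2.488 | Φ(0.843) = 80.1% | Φ(0.528) = 70.1% |
| 604 | 0.02745 | 2.550 | Φ(0.906) = 81.7% | Φ(0.590) = 72.3% |

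Simulation of the Wald interval (400,000 runs, 575 per arm) gives 80.0% and 70.2%. At a true PGS advantage of exactly 7 points, it gives false non-superiority rates of 5.0% and 2.5%.

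**Step 3: where the two rules disagree.** With 604 per arm and SE 2.745 points, non-superiority needs an observed PGS minus IVF difference below:

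- 7 − 1.96 × 2.745 = **+1.6 points** (two-sided 95% CI);
- 7 − 1.645 × 2.745 = **+2.5 points** (two-sided 90% CI).

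A result inside this band, about 0.9 points wide, is non-superior under the sizing level and not under 9.5. The SE here is taken at 65% in both arms; the observed SE would move the limits slightly.

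**The case against.** The strongest reply is that one-sided 5% was in the protocol from the start. It stands in the synopsis and in 9.3, within the same single version as 9.5. The final analysis therefore used the level on which the trial was sized, stated that sizing basis beside the 90% interval, and disclosed the change. All of that stands. A difference between a summary of changes and current text is not an error in itself, and the 90% interval is not the defect.

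Three stronger readings are tempting, and the documents do not support them:

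- **That the final analysis doubled the error rate.** The rise from 2.5% to 5% is real only relative to 9.5. Relative to 9.3 and the synopsis nothing rose.
- **That 9.5 is the pre-enrolment rule and the 90% interval a later invention.** The original plan holds both levels, and nothing in it says which section outranks the other.
- **That the interval was chosen after seeing data.** Nothing shows this. The 5% level is in the dated 2017 protocol. The documents do not show when the reporting interval was changed, so the absence of a date leaves the question open without answering it.

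A further reply is that about 70% is the least favourable figure. This is partly right. Analysing all 604 per arm by intention to treat gives 72.3%. If PGS were truly 1 or 2 points worse, the 9.5 rule would have 80.9% or 88.9% power even with 575, and the synopsis does expect PGS to be unlikely to exceed control. But the sample size rests on equality at 65%, so the stated 80% has to be judged there.

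Last, 575 and 1208 are not miscalculated. Both reproduce. The fault is a mismatch between sections.

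**Conclusion.** The concern holds as an inconsistency in the pre-enrolment protocol. The synopsis and 9.3 use a one-sided 5% error. Section 9.5 and the opening statistical text, read in the ordinary way, use 2.5%. Under the 9.5 rule the stated 80% power is about 70% (575 per arm) to 72% (604 per arm), and 80% would need 729 per arm. The conclusion depends on the choice only if the observed difference lies between about +1.6 and +2.5 points. The documents report no result, so whether this happened cannot be judged from them.

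The final analysis agrees with the sizing level and is less strict than 9.5. What is missing is the justification and amendment that 9.5 calls for: the change is described, but with no reason or date, and the protocol is said to have one version only.

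The figures assume 65% live birth in both groups, a normal-approximation interval, and a two-sided reading of 9.5. That last assumption is an inference, though a well-supported one.

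**What to change.** 1. Name one interval and one one-sided alpha, in the same words, in the synopsis, 9.3, 9.5 and the Final statistical analysis. Either level can be defended if it is used throughout.
2. State power for both: 80% with the two-sided 90% CI (one-sided 5%), and about 70–72% with the two-sided 95% CI (one-sided 2.5%).
3. Report the primary risk difference with both intervals and say whether the non-superiority conclusion is the same under each.
4. Record the reason for the change and its date, as 9.5 requires, and acknowledge that one-sided 5% was already specified in 9.3 and the synopsis.

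The cost is wording in the plan and report plus one extra interval. No further patients are needed. The stated power looks less favourable under the 95% rule. If the two intervals agree, the primary conclusion is stronger for it; if they differ, readers need to know.

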If the viability of the scheduled embryo is severely impaired or lost after thaw, the next one will follow; and if all study-specific embryos (up to N = 3) in both groups lose viability, the surplus embryos will be thawed subsequently for detection or transfer, however, such embryo transfers will not be included in this study.

5) Pregnancy evaluation and follow-up

Serum quantitative hCG will be measured to determine pregnancy 2 weeks after embryo transfer. If a biochemical pregnancy has been achieved, transvaginal ultrasound scan will be performed 35 days after embryo transfer to evaluate for clinical pregnancy. If a clinical pregnancy has been achieved, ultrasound scan will be repeated at 11 weeks gestation to confirm ongoing pregnancy. The subsequent follow-ups will be implemented every three months and continue until termination or delivery.

The cumulative pregnancy outcomes will be followed up after transfers of all euploid embryos in the PGS group and up to 3 blastocysts in the IVF group within 1 year after randomization in both groups if the study-specific embryo transfers are not finished.

Nonviable pregnancy is defined as a crown-rump length  $\geq 7$  mm but no heartbeat or mean sac diameter  $\geq 25$  mm but no embryo or absence of embryo with heartbeat 11 days or 2 weeks later after a gestational sac is detected with ultrasound scan. Complete spontaneous miscarriage refers to complete spontaneous pregnancy loss without curettage or medical abortion after a clinical pregnancy is confirmed. For women who end up with pregnancy loss, subsequent frozen embryo transfer will be scheduled 3 months later if there are study-specific blastocysts left.

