### 6.2.3 Intervention Discontinuation Evaluations

After randomization, further participation in the study will be discontinued in the following situations: a) no euploid embryo is obtained in patients assigned to the PGS group after NGS test; b) Subjects who run out of the protocol-specified embryos; c) Subjects who do not complete transfers of the protocol-specified embryos within 1 year after randomization. Subjects who conceive will be followed to the termination of the pregnancy.

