## 9 STATISTICAL CONSIDERATIONS

### 9.1 General Design Issues

This is a multicenter randomized controlled trial comparing the benefit and safety of PGS and conventional IVF in women with good prognosis. Subjects will be randomly assigned to 2 parallel groups with 1:1 ratio. This study is designed as a non-superiority study to test the following primary and secondary hypothesis.

- a) The primary hypothesis is that PGS will result in a similar cumulative live birth after up to 3 transfers within 1 year after randomization compared with conventional IVF.
- b) The secondary hypotheses are as follows:
  - 1) PGS will be more likely to yield a Good Birth Outcome.

- 2) PGS will reduce the rate of pregnancy loss.
- 3) The incidence of other maternal and neonatal complications will be comparable between PGS and IVF groups.
- 4) The rate of multiple pregnancy will be comparable between PGS and IVF groups
- 5) The birth weight will be comparable between babies resulted from PGS and IVF.
- 6) PGS will require fewer embryo transfers before achieving live birth.

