### 9.2.2 Secondary outcomes:

The secondary outcomes include the Good Birth Outcome rate (defined as a live birth of an infant born at  $\geq 37$  weeks, with a birth weight between 2500 and 4000g and without a major congenital anomaly), cumulative pregnancy rate, cumulative pregnancy loss rate, multiple pregnancy rate, duration of pregnancy, birth weight, cumulative incidence of maternal and neonatal complications, and number of embryo transfers to achieve live birth.

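### The test of secondary hypothesis 6 (fewer transfers to live birth with PGS) favours PGS by construction, because PGS women have fewer embryos available to transfer

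*Combined protocol and SAP*

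**What the plan says.** Section 9.2.2 lists as a secondary outcome the "number of embryo transfers to achieve live birth". Sections 1.2 and 9.1 attach a directional hypothesis to it, the sixth: "PGS will require fewer embryo transfers before achieving live birth". Section 9.5 gives the analysis: "birth weight and times of embryo transfer will be tested by student t test", or by a non-parametric test where needed. Neither section gives a denominator or a rule for women who have no live birth or no embryo to transfer.

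The supply of embryos differs by arm. Section 5.3.1, item 5, follows outcomes over transfers of "all euploid embryos in the PGS group and up to 3 blastocysts in the IVF group within 1 year after randomization". Section 5.1.3 withholds mosaic embryos, and section 6.2.3 ends participation for PGS women with no euploid embryo. One small exception works the other way: under section 5.1.3, an embryo whose amplification fails may still be transferred.

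The section headed Final statistical analysis does not mention the number of transfers. It adds that "Kaplan-Meier curves were used for the time to live birth", and that outcomes were analysed for the first, second and third transfers.

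**The concern.** Hypothesis 6 is meant to show that genetic selection reaches a live birth more efficiently. The planned count cannot show that. An IVF woman can succeed at transfer 1, 2 or 3. A PGS woman with one euploid embryo can succeed only at transfer 1, and one with two can succeed only at transfer 1 or 2. The late successes that raise the IVF mean are removed from the PGS arm because embryos were discarded, whether or not the right ones were discarded.

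Any procedure that discards embryos would thus tend to confirm the hypothesis, including one that lowers the chance of a live birth. The statement that PGS needs fewer transfers could then be reported as a benefit of PGS on evidence that does not bear on it.

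**Working it through.** **The plan's own figures.** The documents give no figure for this outcome. The primary sample size reproduces: 2 × 0.65 × 0.35 × (1.645 + 0.842)² / 0.07² = 574.1, so 575 per group, and 1150 × 1.05 = 1207.5, so 1208 in total, or 604 per arm.

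**Inputs from the protocol.** Euploidy is about 60% per blastocyst (section 2.1). Control cumulative live birth is 65% after three transfers (section 9.3).

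**Assumptions not in the documents.** Live birth is 30% at every transfer, since 1 − 0.7³ = 65.7%, close to 65%. The test is useless: each embryo is labelled transferable with probability 0.6, regardless of its potential. All available embryos are used until live birth.

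**Embryo supply with PGS.** Binomial(3, 0.6) gives 0, 1, 2 or 3 transferable embryos in 6.4%, 28.8%, 43.2% and 21.6% of women, mean 1.8. At least 1, 2 or 3 are available in 0.936, 0.648 and 0.216.

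**Probability of live birth at transfer t.** IVF: 0.3 × 0.7^(t−1). PGS: the same, times the probability of having at least t embryos.

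| Transfer | IVF | PGS |
|---|---|---|
| 1 | 0.300 | 0.300 × 0.936 = 0.281 |
| 2 | 0.210 | 0.210 × 0.648 = 0.136 |
| 3 | 0.147 | 0.147 × 0.216 = 0.032 |
| Total | 0.657 | 0.449 |

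**Mean transfers among women with live birth.**
- IVF: (0.300 + 2 × 0.210 + 3 × 0.147) / 0.657 = 1.77, SD 0.79
- PGS: (0.281 + 2 × 0.136 + 3 × 0.032) / 0.449 = 1.45, SD 0.62
- Difference: −0.32. With 604 per arm there are about 397 and 271 live births, so SE = √(0.79²/397 + 0.62²/271) = 0.055 and t is about 5.9.

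**Other denominators.** Transfers per randomised woman are 1 + 0.7 + 0.49 = 2.19 with IVF and 0.936 + 0.7 × 0.648 + 0.49 × 0.216 = 1.50 with PGS, a gap of −0.69. Among women with at least one transfer, PGS has 1.50/0.936 = 1.60, a gap of −0.59. Both gaps are larger than the one among live births.

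**Other test.** In 4000 simulated trials of the useless test (575 per arm, success set to 29.5% so that IVF reaches exactly 65%), the Mann-Whitney test among live births favoured PGS significantly in 99.95%. The choice of test does not matter.

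**Sensitivity.** Useless test, 575 per arm, women with live birth. Except where stated, euploidy is 60% and success is 29.5% per transfer.

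| Assumption changed | Difference (PGS − IVF) | Trials significant for PGS |
|---|---|---|
| Euploidy 40% | −0.48 | about 100% |
| Euploidy 66% | −0.28 | 99.8% |
| Euploidy 80% | −0.16 | 82% |
| 80% go on to each next transfer | −0.27 | 99.8% |
| 50% go on to each next transfer | −0.17 | 90% |
| Success by morphology rank 0.40/0.28/0.19 | −0.21 | 99% |
| Success by morphology rank 0.50/0.20/0.125 | −0.12 | 80% |
| Prognosis varies between women (beta, precision 2 or 5) | −0.23 or −0.28 | at least 99.5% |

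**Why the direction holds.** If the label carries no information and success does not depend on rank, the PGS-to-IVF ratio at transfer t is the probability of having at least t embryos (0.936, 0.648, 0.216). It falls with t whatever the success rate and however much women differ. For success falling with rank, the direction rests on the two cases enumerated.

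**Against a perfect test.** If all live births come from euploid embryos, success is 0.295/0.6 = 0.492 per euploid transfer. Both arms then reach 65%, and the difference is −0.44. A useless test gives about three quarters of that (0.32/0.44).

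**The case against.** **The primary outcome guards against this.** Section 9.2.1 counts live birth over all women randomised, and live birth after the first transfer is a tertiary outcome. A loss of about 20 points would be plain. This stands, and it confines the harm to the claim on hypothesis 6. A reader might infer that the primary conclusion or sample size is threatened; neither is.

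**Fewer transfers is a real saving for the woman.** As a description of treatment burden, that is fair. But the hypothesis concerns transfers needed to reach a live birth, and a lower count caused by having nothing left to transfer does not support it.

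**The plan allows a non-parametric test.** True, so the t test itself is not the fault. The rank test shares the bias.

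**The plan does not say that women without live birth are excluded.** Also true. The outcome's name suggests it, but section 9.5 is silent. The point does not rest on that reading, since counting all women widens the gap.

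**The size depends on assumptions.** It does. Constant success and random labelling are not in the documents. Transfer of embryos with failed amplification would raise PGS supply somewhat; the 80% row indicates the effect of a larger supply.

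**A stronger reading of the time-to-event curves.** Section 6.2.3 ends participation for "Subjects who run out of the protocol-specified embryos". A reader might infer that such women were censored in the Kaplan-Meier analysis and that this flatters PGS. The documents do not support that. The final analysis text states no censoring rule, section 6.2.3 lists reasons for discontinuation rather than for censoring, and running out of embryos applies to both arms. What remains is an unstated rule, not a demonstrated error.

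**Conclusion.** The point holds for the number-of-transfers outcome. Its denominator is undefined, and under each natural choice the unequal embryo supply makes the count lower with PGS even if the genetic test is worthless. In the base case the difference among live births is −0.32 (1.45 against 1.77, t about 5.9), with cumulative live birth of 44.9% against 65.7%. Across the assumptions examined on euploidy, morphology rank, prognosis and continuation, the difference runs from about −0.12 to −0.48, and about 80% or more of trials would be significant. The direction follows from the design; the size depends on the stated assumptions. The consequence is a likely false confirmation of secondary hypothesis 6. The change should be made, but the primary analysis does not depend on it.

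**What to change.** Test hypothesis 6 by the cumulative proportion of all randomised women with live birth by transfer 1, 2 and 3, with a risk difference and confidence interval at each. Women with no embryo to transfer count as having no live birth. Label the mean number of transfers among live births as descriptive only.

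This separates the two cases:
- **Useless test (30% per transfer):** PGS 28.1/41.7/44.9% against IVF 30.0/51.0/65.7%. PGS shows no gain at any step.
- **Perfect test (29.5% per untested transfer):** PGS 46.1/62.3/65.0% against IVF 29.5/50.3/65.0%. PGS shows a clear early gain.

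Total transfers divided by live births is a tempting replacement but should not be used. It is 3.33 in both arms under constant success (2.19/0.657 and 1.495/0.449). When prognosis varies between women, it favours a useless test: 2.84 for PGS against 3.13 for IVF at beta precision 2, and 3.10 against 3.26 at precision 5.

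For time to live birth, state that women with no remaining study embryos stay event-free in the risk set to the end of follow-up, in both arms.

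The data are already collected. The cost is SAP wording, minor programming and a possibly less favourable result for hypothesis 6.
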